## Abstract

**Background:**

Few large randomized controlled trials provide strong evidence to guide surgical repair of primary rhegmatogenous retinal detachment (RRD) repair. The purpose of this factorial, single-blind, randomized controlled trial is to analyze and compare the surgical outcomes, functional visual outcomes, complications, and quality of life associated with RRD repair using (A) pars plana vitrectomy only (PPV) or PPV with scleral buckle (PPV-SB) and (B) sulfur hexafluoride gas (SF_6_) or perfluoropropane gas (C_3_F_8_) tamponade.

**Methods:**

Eligible patients with moderately complex RRD will be randomized 1:1 to PPV or PPV-SB and 1:1 to SF_6_ or C_3_F_8_ gas tamponade. Approximately 560 patients will be recruited to be able to detect a difference of around 10% in SSAS rate between the groups. Patients will be followed using multimodal imaging and quality of life questionnaires after the surgical repair until 1 year postoperative. The primary outcome will be a single-surgery anatomic success (SSAS), defined as the absence of reoperation for recurrent RRD in the operating room. Secondary outcomes will be pinhole visual acuity (PHVA) at 8–10 weeks and 6 months, final best-corrected visual acuity (BCVA), final retina status (i.e., attached or detached), time to onset of RRD recurrence, severity and number of complications, and questionnaire results.

**Discussion:**

This will be the first 2 × 2 factorial RCT examining repair techniques in primary RRD. It will also be the first RCT to compare gas tamponade between the two most common agents. Notably, it will be adequately powered to detect a clinically significant effect size. The use of multimodal imaging will also be a novel aspect of this study, allowing us to compare head-to-head the impact of adding an SB to the retina’s recovery after RRD repair and of differing gas tamponades. Until now, the treatment of RRD has been largely guided by pragmatic retrospective cohort studies. There is a lack of strong evidence guiding therapeutic decisions and this trial will address (1) whether supplemental SB is justified and (2) whether longer duration gas tamponade with C_3_F_8_ is necessary.

**Trial registration:**

ClinicalTrials.gov NCT05863312. Registered on 18 May 2023.

**Supplementary Information:**

The online version contains supplementary material available at 10.1186/s13063-023-07815-x.

## Introduction

### Background and rationale {6a}

Two important and common techniques used in the surgical repair of rhegmatogenous retinal detachment (RRD) are pars plana vitrectomy (PPV) and scleral buckle (SB). Both can be used alone or in combination with a gradual shift towards PPV with improvements in technology and technique. Prominent retrospective cohort studies such as the Primary Retinal Detachment Outcomes (PRO) study suggest that a combination of PPV and SB (PPV-SB) has an advantage over PPV alone for phakic and pseudophakic patients [1, 2]. Similarly, a meta-analysis of cohort studies suggests that there may be an increased rate of surgical success without reoperation in patients receiving PPV-SB [3]. However, the few randomized controlled trials (RCT) with small sample sizes (range 30 to 100 patients per group) and heterogenous surgical techniques looking into this question have not found an advantage to additional SB [4–7], and a recent meta-analysis of RCT has also not found an advantage but rather increased myopization, duration of surgery, and postoperative pain following additional SB [8]. In a way to simulate randomization, we performed a propensity score analysis comparing the surgical outcomes of PPV compared to PPV-SB at our center which also showed similar results between both techniques [9]. The discrepancy between the results of non-randomized and randomized studies in this debate is likely due to indication bias, that is, the tendency of surgeons to treat more complex patients using PPV-SB thinking that it will provide them with a better outcome.

In addition to this choice of surgical technique, there is also the use of different gas tamponades which can be of interest. Most commonly, vitreoretinal surgeons use either sulfur hexafluoride gas (SF_6_) or perfluoropropane gas (C_3_F_8_) to maintain the reapproximation of the retina postoperatively, reserving the use of silicone oil to refractory cases where a longer tamponade is needed. SF_6_ remains in the eye for 2 to 3 weeks, while C_3_F_8_ remains in the eye for 6 to 8 weeks. There may therefore be an indication bias to use C_3_F_8_ in more complex cases where a longer tamponade duration is desired. Unfortunately, there are no RCT comparing these two tamponade agents, while studies comparing air and gas tamponades have had mixed results [10, 11].

### Objectives {7}

The objective of this study is to analyze and compare the surgical outcomes, functional visual outcomes, complications, and quality of life associated with primary RRD repair using (A) PPV or PPV-SB (primary objective) and (B) SF_6_ and C_3_F_8_ gas tamponade (secondary objective). Our working hypotheses are as follows:PPV and PPV-SB have similar single-surgery anatomic success (SSAS) rate.PPV may lead to better final best-corrected visual acuity (BCVA), less complications, and better quality of life compared to PPV-SB.SF_6_ and C_3_F_8_ gas tamponades have similar SSAS rates, visual outcomes, complications, and quality of life.There is minimal to no significant interaction between surgical technique (i.e., PPV or PPV-SB) and gas tamponade (i.e., SF_6_ and C_3_F_8_).

### Trial design {8}

This is a large, 2 × 2 factorial, interventional, randomized controlled trial. Eligible patients with primary RRD will be randomized using a simple randomization 1:1 to receive PPV or PPV-SB and SF_6_ or C_3_F_8_ gas tamponade. Statistical analyses of the outcomes will aim to demonstrate the superiority of one technique over the other.

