### Outcomes {12}

The primary outcome is SSAS defined as freedom from reoperation for recurrent RRD at all follow-up evaluations. Localized recurrences or new tears treated using a laser in the ambulatory clinic will not be considered a failure of the primary surgery but will be noted. We considered a difference of 10% in SSAS to be clinically relevant for this trial and based the sample size calculation on this threshold of chosen efficacy. Secondary outcomes will include PHVA at 8–10 weeks and 6 months, final BCVA, final retina status (i.e., attached or detached), time to onset of RD recurrence, severity and number of complications, and questionnaire results (see Additional file 1). The principal questionnaire was previously used and validated by Potic et al. [12] with additional questions used to specifically assess possible side effects and reductions in quality-of-life associated with the addition of SB and longer-duration intraocular gases. In cases of primary surgery failure, the cause of recurrence (i.e., PVR including epiretinal membrane (ERM) in the macular area causing recurrent RD, new or recurrent retinal breaks) will be reviewed. The extent of PVR at follow-up will also be evaluated. The duration of surgery will also be collected. Number of additional visits and supplementary laser and intraocular pressure treatments will be evaluated. Complications will be graded using the novel Classification of Ophthalmological Complications (COC; see Table 1).

**Table 1 Tab1:** Classification of ophthalmological complications (COC)

Complication grade	Definition
Grade I	Any deviation from the normal postoperative course without the need for modification of planned pharmacological treatment or surgical intervention Allowed therapeutic regimens are as follows: any previous medication, any medication prescribed routinely (i.e., topical antibiotics, glaucoma drops, anti-inflammatory drops, steroid drops, oral pills), artificial tears, hot compresses, and analgesic drugs (Advil/Tylenol only)
Grade II	Requiring change in planned pharmacological treatment with higher frequency or longer duration of drops or the introduction of new drugs (including autologous serum drops); these can include glaucoma drops and steroid drops and the use of oral drugs other than Advil/Tylenol (e.g., Diamox, prednisone). Also includes YAG capsulotomy

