### Sample size {14}

We based our sample size calculations on the size necessary to detect a clinically significant effect in surgical technique, given that estimates of effect size among gas tamponades are not as precise in the literature and are a secondary purpose of our study. Based on previous results from our center, SSAS is achieved in 92% and 88% of phakic patients undergoing PPV and PPV-SB, respectively, compared to 91% and 90% in pseudophakic patients. We therefore have at most a 4% difference between the treatment groups. In the PRO study reports, SSAS rates differed between PPV and PPV-SB with 83% and 91%, respectively, in phakic patients and 84% and 92% in pseudophakic patients. Based on our previous results, this would yield a small effect size of about 0.13, while this would be approximately 0.25 according to the treatment differences in the PRO study reports. Considering that a treatment difference smaller than what was found in the PRO study could be deemed not clinically significant, we are proposing a total sample size of 560 patients (*n* = 140 per group) which, assuming a 10% drop-off rate, would still allow us to detect an effect size of 0.25 with a power greater than 80% (see Table 3).

**Table 3 Tab3:** Total sample size calculation to detect an effect in the ranges of 0.20 to 0.30 for surgical technique (i.e., PPV and PPV-SB) at various study powers. We are proposing a sample size of 560 patients. Corresponding effect size and power will be achieved for the analysis of gas tamponades (i.e., SF_6_ and C_3_F_8_)

Effect size	Power		
	80%	85%	90%
0.20	784	900	1052
0.25	**504**	**576**	672
0.30	348	400	468

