### Statistical methods

#### Statistical methods for primary and secondary outcomes {20a}

The primary outcome will be compared between the groups using the chi-square test for the difference in rates of SSAS in both the surgical technique and gas tamponade arms of the study. Testing between the groups for secondary outcomes of PHVA at 8–10 weeks and 6 months, final BCVA, final retina status (i.e., attached or detached), time to onset of RD recurrence, severity and number of complications, and questionnaire results will also be performed using adjustments for repeated measures and multiple comparisons as appropriate.

To calculate estimates of the treatment effects and their corresponding 95% confidence intervals (CI), a multiple logistic regression including both surgical technique and gas tamponade will be built for SSAS. Cox proportional hazards and multiple linear regression models will also be built for the time to onset of RD recurrence and final BCVA, respectively. In these analyses, we assume that there is a negligible interaction between surgical technique and gas tamponade. However, appropriate interaction terms will be added to the models to explore this possibility. If this shows negligible interaction, both analyses will be performed independently.

Statistical analyses will be performed using R for Windows (version 3.6.3; R Foundation for Statistical Computing) and IBM SPSS Statistics for Windows (version 27.0; IBM Corp., Armonk, NY). Analyses will be conducted at the 0.05 significance level, except when appropriate for adjustment of multiple comparisons.

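### The protocol hypothesises similar SSAS for both comparisons but plans only to show superiority, and no rule says when an interval would support similarity

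*Protocol article*

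**What the plan says.** All references are to the protocol article.

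- **Objectives {7}**: the first working hypothesis is "PPV and PPV-SB have similar single-surgery anatomic success (SSAS) rate". For SF6 and C3F8 the expectation is that the "gas tamponades have similar SSAS rates, visual outcomes, complications, and quality of life". A separate hypothesis is that PPV may do better on BCVA, complications and quality of life.
- **Trial design {8}**: "Statistical analyses of the outcomes will aim to demonstrate the superiority of one technique over the other".
- **Outcomes {12}**: "We considered a difference of 10% in SSAS to be clinically relevant for this trial".
- **Sample size {14}**: "we are proposing a total sample size of 560 patients", which after 10% drop-off "would still allow us to detect an effect size of 0.25 with a power greater than 80" per cent. The same section says that a difference smaller than the PRO study's could be regarded as not clinically significant. That difference is 8 points (83% v 91%, 84% v 92%).
- **Statistical methods {20a}**: "The primary outcome will be compared between the groups using the chi-square test for the difference in rates of SSAS", for both factors. Effects and 95% CIs come from a logistic regression holding both factors; no effect scale is named. "Analyses will be conducted at the 0.05 significance level, except when appropriate for adjustment of multiple comparisons".
- **Interim analyses {21b}**: the rule also looks for a significant difference, of more than 10%.

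**The concern.** On the primary outcome, the hypothesis and the inferential aim point in opposite directions. The investigators expect similarity, while every stated decision step asks whether a difference can be shown. The Discussion says the trial will address whether a supplemental buckle is justified and whether the longer-acting gas is necessary. A negative answer to either question needs evidence that any loss of SSAS is smaller than what matters clinically, and a non-significant chi-square test does not provide that evidence.

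If the centre's own earlier results are right, a non-significant test is the most likely outcome. The plan does not say what may then be concluded. If the margin for similarity is chosen after the data are seen, the conclusion will not be credible.

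**Working it through.** **Inputs.** Total 560, 1:1 on each factor, so 280 per level; less 10% drop-off, 280 × 0.9 = 252. Alpha 0.05, taken as two-sided. SSAS rates from Sample size {14}: own centre 92% v 88% and 91% v 90%; PRO study 91% v 83% and 92% v 84%. The common rate of 90% v 90% is an assumption, close to the centre's figures.

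**1. The plan's own figures reproduce.** With h = 2·asin(√p1) − 2·asin(√p2):
- 92% v 88%: h = 0.134 (stated about 0.13).
- PRO rates: h = 0.241 and 0.250 (stated about 0.25).
- n per level = 2(1.96 + 0.842)²/0.25² = 251.2, so 252; total 504; 504/0.9 = 560. Power at h = 0.25 with 252 per level is 80.1%.

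The sample size is right for a superiority test.

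**2. How often the test is non-significant.** Exact binomial enumeration of the uncorrected chi-square test, 252 per level:

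| True SSAS | Power | Non-significant |
|---|---|---|
| 92% v 88% | 31.9% | 68% |
| 91% v 90% | 6.6% | 93% |
| 91% v 83% | 76.9% | 23% |
| 92% v 84% | 79.7% | 20% |

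The last two rows are the ordinary type II error of a trial with about 80% power. The table shows that non-significance occurs under both competing views, so it does not separate them.

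**3. What the interval can show.** At 90% v 90%, SE = √(2 × 0.9 × 0.1/252) = 0.0267, and the 95% half-width is 1.96 × 0.0267 = 5.2 points. An observed difference just short of significance therefore has an interval reaching about 2 × 5.24 = 10.5 points, past the 10 points of Outcomes {12}.

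**4. Chance that the whole 95% CI for the risk difference lies within ±m.** The normal approximation for true difference d is Φ((m − d)/SE − 1.96) − Φ((−m − d)/SE + 1.96).
- 90% v 90%, m = 0.10: 2Φ(3.74 − 1.96) − 1 = 0.925.
- 92% v 88%: SE = √((0.0736 + 0.1056)/252) = 0.0267. With m = 0.10: Φ(2.25 − 1.96) − Φ(−5.25 + 1.96) = 0.614.

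Exact enumeration with Wald intervals:

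| True SSAS | Within ±10 | Within ±8 |
|---|---|---|
| 90% v 90% | 92% | 70% |
| 92% v 88% | 62% | 33% |
| 91% v 83% | 10.5% | 2.7% |

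**5. Non-significant results whose interval still crosses ±10 points.** About 3% of them at 90% v 90%, about 11% at 92% v 88%, and about 55% at 91% v 83%. Non-significance is thus least informative when the PRO-sized difference is real.

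**The case against.** The strongest reply is that this is a coherent superiority trial. The aim, sample size, test and interim rule agree with each other, and the Discussion says the trial is powered for the PRO effect if that effect truly exists. On this view the working hypotheses record an expectation and are not the statistical hypotheses, and whether a buckle earns its place can be put as a superiority question. Superiority testing also suits the hypothesis that PPV is better on BCVA, complications and quality of life. All of this stands as a defence of the test. It does not supply a way to conclude similarity on SSAS, which the Objectives put first.

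Several stronger readings are tempting but not supported:

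- **That a failed test is the only information on similarity.** Statistical methods {20a} also plans 95% CIs. What is missing is a link between those intervals and a margin.
- **That the protocol will report non-significance as similarity.** No section says so.
- **That the interval is fixed on the odds-ratio scale.** Logistic regression is named but the scale of the reported effect is not, and an article may leave that to the analysis plan.
- **That the present sample settles similarity at no cost.** That holds only for nearly equal rates and the wider margin, as step 4 shows.

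It is also fair to say that, near equality, a plain interval read against ±10 points would usually resolve a non-significant result. That argues for stating the rule.

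**Conclusion.** The mismatch stands and should be fixed. It is stated in the document and is not merely a detail left to an analysis plan: the Objectives hypothesise similar SSAS for both factors, and Trial design fixes superiority as the aim. Followed as written, the plan gives its authors' expected primary result (68% to 93% likely at their own centre's rates) no defined route to the conclusion they hypothesise.

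The randomisation, the superiority test and the sample size are not put in doubt.

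The choice of margin matters. Outcomes {12} names 10 points, while Sample size {14} treats the PRO difference of 8 points as the threshold. A ±10 margin is wider than that difference and would declare similarity in about 10.5% of trials at a true 91% v 83%; ±8 brings this to 2.7% but lowers the chance of success.

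These figures assume 252 evaluable patients per level, negligible interaction between the factors, a two-sided 0.05 level and Wald intervals. Simple randomisation will make the levels slightly unequal.

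**What to change.** 1. Reconcile Objectives {7} with Trial design {8}, so that similarity on SSAS is either an expectation only or a claim with its own rule.
2. Keep the two-sided superiority test.
3. In Trial design {8} and Statistical methods {20a}, make the SSAS risk difference with 95% CI the primary estimate for each factor. It can be standardised from the planned logistic model.
4. Reconcile the 10 points of Outcomes {12} with the PRO-sized 8 points of Sample size {14}, and fix one margin before the mid-recruitment interim analysis or any other unblinded look. The value is a clinical choice for the trial team.
5. Claim similarity only if the whole interval lies within the margin. Otherwise report a non-significant result as inconclusive.
6. State the operating characteristics from step 4 for the chosen margin, including those at 92% v 88% and 91% v 83%.

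The cost is protocol and analysis-plan wording, with no extra patients or data. The downside is that some non-significant results must be called inconclusive. With a ±8 margin that would be common: even with equal true rates of 90%, about 30% of trials would not meet the rule.

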## Methods: participants, interventions and outcomes

### Study setting {9}

The study will take place at the Centre Hospitalier Universitaire de Québec – Université Laval, a tertiary care, academic center in Québec City, Canada.

### Eligibility criteria {10}

Patients aged ≥ 18 years diagnosed with RRD will be considered for inclusion. Since very simple RRD are more likely to be treated with PPV, while more complex RRD are more likely to be treated with PPV-SB, we will select patients who have a moderately complex RRD, like the PRO study. This excludes the following characteristics: proliferative vitreoretinopathy (PVR) grade ≥ C2, chronic RRD with duration > 3 months, proliferative diabetic retinopathy with tractional retinal detachment (RD), macular holes, epiretinal membrane grade 3 or 4, traumatic RD, giant retinal tears, retinal dialysis, foveoschisis, wet age-related macular degeneration, endophthalmitis, acute retinal necrosis, Coats disease, retinopathy of prematurity, retinoschisis, retinal colobomas, prior glaucoma surgery or strabismus surgery (difficulty with adding SB), and superior RD extent less than 3 clock hours (favoring PPV).

Age younger than 45 years is a relative exclusion factor whereby, if the surgeon considers the patient more eligible for an SB-only procedure, they will not be considered for the study. In contrast to the PRO study, we will accept moderate degrees of PVR and RD extent greater than 9 clock hours (favoring PPV-SB). We also did not consider certain factors which were included given that the PRO study also included SB-only procedures (e.g., significant vitreous opacities, cataract, prior vitrectomy, greater than moderate vitreous hemorrhage).

### Who will take informed consent? {26a}

Designated research team members will be tasked with explaining trial details and obtaining written informed consent from eligible patients after being presented with the study by members of the clinical care team.

### Additional consent provisions for collection and use of participant data and biological specimens {26b}

Vitreous samples could be collected as part of a biobank at the center for which a separate, parallel consent process will be used.

### Interventions

#### Explanation for the choice of comparators {6b}

Currently, PPV and PPV-SB are both commonly used procedures for the repair of simple RRD and differences differ between centers and practitioners. The use of SF_6_ or C_3_F_8_ gas tamponades is also often left to the surgeon’s discretion. Both procedures will therefore be compared in this trial. The current standard of care involves the operating surgeon choosing whether to place an SB or not, as well as whether to place SF_6_ or C_3_F_8_ according to their personal preference. This is only guided by expert opinion at the moment in the absence of high-grade evidence; hence, this justifies the relevance of this study to better support decisions in practice.

#### Intervention description {11a}

Surgery will be performed under local anesthesia with retrobulbar block (5 to 10 cc of 2% lidocaine without epinephrine and 0.5% bupivacaine in a 1:1 ratio). In all cases, surgery will be performed using a wide-angle viewing system and the Alcon Constellation System (Alcon Laboratories, Inc., Fort Worth, TX) combined with the ULTRAVIT 23-G + or 25-G + vitreous cutter (Alcon).

Pars plana vitrectomy will be performed in a standard fashion starting with central vitrectomy, then by localizing retinal breaks and marking them with endodiathermy. Perfluorocarbon will be used to displace subretinal fluid which will be aspirated at its exit from the retinal break as much as possible to avoid retinal pigment epithelium (RPE) dispersion into the vitreous and maximal vitreous base shaving will be performed in all cases. This will be followed by an air-fluid exchange. The use of cryotherapy to solidify the retina intraoperatively and the use of internal limiting membrane peeling of the posterior pole will be at the discretion of the surgeon. In all cases, laser photocoagulation around retinal breaks, holes, areas of lattice degeneration, and posterior to sclerotomy sites will be done and then a 360° laser retinopexy will be performed at the surgeon’s discretion and consisted of three rows of medium-white burns anterior to the level of the vortex vein, towards and beyond the equator. In cases with SB, after 360° peritomy and dissection in 4 quadrants, a 41-circling band with 3082 sleeves (Labtician Ophthalmics, Oakville, ON, Canada) will be used in all cases and fixed to the sclera at approximately 11.5 mm from the limbus (or 5.5 from the insertion of rectus muscles) using partial thickness scleral tunnel or mattress sutures with 5.0 prolene or nylon performed in four quadrants depending on the surgeon preferences. At the end of the surgery, a gas tamponade will be injected inside the eye, either SF_6_ or C_3_F_8_. The surgical technique at the second surgery, if applicable, will be at the discretion of the treating surgeon.

